### Supporting measures

At baseline, participants complete a demographic questionnaire assessing age, race, ethnicity, history of intentional weight loss, and weight history. Literacy is assessed using the Newest Vital Sign [125]. Information on food security and acculturation, parity, and intervals between pregnancies are also collected to assess any prior relationship with postpartum weight retention [126-129]. Information on changes in smoking, prescription medications, unsafe dieting practices [78], job status, and participation in other weight loss programs are assessed at follow-up assessments. Participants are also asked at each follow-up assessment to report all prescription and non-prescription medication, and to indicate any health problems that they have experienced since the last assessment. Breastfeeding intensity and duration [2], and information about introduction of formula, are also assessed at each visit. Similar to our prior research, safety assessments include injuries due to physical activity, instances of extreme hunger, fatigue, and changes in milk supply.

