#### Analysis plan

The primary outcome measure, change in weight from baseline over time, is assessed at six and 12 months. All measured weights will be included in the analyses. The analysis strategy is based on a conceptual framework that explicitly recognizes that both differences between individuals within clinics and between clinics may contribute to variance in weight change. Randomly assigned group (standard care versus intervention) is the main independent variable for intention-to-treat (ITT) analyses. County is a stratification variable for randomization and is expected to be balanced across intervention and standard care groups by design. Our analysis approach uses linear mixed-effect models to analyze differences between the intervention and standard care clinics allowing for within-cluster variation (participants within the same clinic) and within-individual variation (repeated measures) [132]. The model will include factors for a fixed effect for treatment and group and random effects for clinic as well as a group × time interaction term to test if the change over time in the dependent variable differs significantly for the two study groups. In addition, for primary and secondary outcomes, the model will include participant-level covariates to adjust for any baseline differences, or adjust for covariates that may relate to the outcome, including lactation, age, age at menarche, education, income, smoking status, language, socioeconomic status, race and ethnicity, height, pre-pregnancy BMI, parity, gestational gain, inter-pregnancy interval, baseline BMI, and changes in marital status and employment [2,133-139] In addition, the model will include terms to account for whole-clinic (cluster-level) variants, including Latina proportion, lactation proportion, mean age, mean education, and mean SES.

Our study design will give rise to temporally repeated measurements, and some subjects may be lost to follow up. In the primary analysis, missing weight measurements will be assumed missing at random, but diagnostic analyses will be conducted related to missing data (for example, comparing baseline characteristics of completers versus non-completers and creating propensity scores). If missing data appear to have the potential of influencing interpretation, we will also conduct multiple imputations using several different models for non-ignorable missingness. These will be used to assess the range of impact that missing data may exert on our results.

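### The primary intention-to-treat model adjusts for changes in marital status and employment, which arise after randomisation and can bias the treatment effect in either direction

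*Protocol article*

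**What the plan says.** The Analysis plan defines the outcome: "The primary outcome measure, change in weight from baseline over time, is assessed at six and 12 months". It names the estimation principle: "Randomly assigned group (standard care versus intervention) is the main independent variable for intention-to-treat (ITT) analyses". It then sets out the adjustment: "for primary and secondary outcomes, the model will include participant-level covariates to adjust for any baseline differences, or adjust for covariates that may relate" (that is, have a bearing on the endpoint). The list that follows includes "including lactation, age, age at menarche, education, income, smoking status, language" and closes with "inter-pregnancy interval, baseline BMI, and changes in marital status and employment".

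Supporting measures says when some of these items are collected. A sentence opening "Information on changes in smoking, prescription medications" also covers job status and assigns all its items to the follow-up assessments. On lactation it says: "Breastfeeding intensity and duration [2], and information about introduction of formula, are also assessed at each visit". It does not say when marital status is collected.

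On missing data, the Analysis plan says that in the primary analysis "missing weight measurements will be assumed missing at random". It also says that every measured weight will be used. It gives no rule for missing covariate values.

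**The concern.** An intention-to-treat comparison estimates the total effect of assignment. Randomisation balances what exists before assignment and does not protect what happens afterwards. If the programme influences whether a woman takes, leaves or changes work, or whether her household changes, then holding those changes fixed removes whatever part of the effect passes through them. If such a change and weight share an unmeasured cause, such as stress or health, conditioning on it can also create an association between arm and weight where none exists. The two mechanisms can push the estimate in opposite directions.

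The plan itself allows that variables of this kind may carry the effect: a later paragraph of the Analysis plan proposes to test mediation by demographic as well as behavioural and psychosocial factors. The commitment also spreads, because the model for reaching preconception weight and the models for behavioural and psychosocial outcomes reuse the same specification.

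A second, smaller matter is completeness. A change variable needs a follow-up value, so it can be missing where baseline covariates are not.

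**Working it through.** **Step 1. Is a post-randomisation covariate really in the primary model?**
- The list is introduced as part of the model for primary and secondary outcomes, in definite terms.
- The list marks body mass index as a baseline value and marks marital status and employment as changes, so the authors distinguish timing where they name it.
- Supporting measures collects job status at follow-up. For employment the text therefore settles the timing. For marital status no collection time is given, but a change from baseline can only be seen later.

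The answer is yes: employment by direct text, marital status by its wording.

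**Step 2. Reproduce the plan's own power figure, to have a scale.** Inputs from Sample size calculation: 12 clinics of 34 women, difference 2 kg, standard deviation 4.5 kg, intraclass correlation 0.02, two-sided 0.05, 30% attrition.
- Women per clinic at 12 months: 34 × 0.7 = 23.8. Per arm: 6 × 23.8 = 142.8.
- Design effect: 1 + (23.8 − 1) × 0.02 = 1.456.
- Standard error of the difference: 4.5 × √(2 × 1.456 / 142.8) = 0.643 kg.
- Noncentrality: 2 / 0.643 = 3.11. Power is 80.1% with a t-test on 10 cluster degrees of freedom (12 − 2), and 87.5% by the normal approximation.

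Both agree with the stated figure of at least 80%. The calculation uses no covariates, so removing some does not change it.

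**Step 3. How far could the adjustment move the estimate?** The document gives no inputs, so all parameters here are assumptions. They are: total effect −2 kg, standard deviation 4.5 kg, a binary change variable present in 30% of controls, and 2,000,000 simulated records. Where the change variable affects weight, it does so by 1.5 kg. Where there is a shared cause, it moves weight by 1.5 kg per standard deviation and has a loading of 0.5 on the change variable.

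| Assumed structure | Adjusted estimate (kg) |
|---|---|
| Arm does not affect the change variable | −2.00 |
| Arm shifts it by 10 points; it affects weight | −1.85 |
| Arm shifts it by 20 points; it affects weight | −1.70 |
| 10 points, with a shared cause as well | −1.98 |
| 20 points, with a shared cause as well | −1.94 |
| 20 points, shared cause only | −2.25 |

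The rows with a pure pathway follow by hand: 2 − 0.10 × 1.5 = 1.85 and 2 − 0.20 × 1.5 = 1.70. The largest shift is 0.30 kg, which is 0.30 / 2 = 15% of the target and 0.30 / 0.643 = 0.47 standard errors.

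**Step 4. What that means for power.** With the standard error held at 0.643 kg and 10 degrees of freedom, an expected estimate of 1.85 kg gives 73.7% power and 1.70 kg gives 66.5%, against 80.1% at 2 kg. A shift the other way overstates the benefit.

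**Step 5. Missing covariate values.** A woman with no follow-up weight has no change in weight to analyse, so these covariates cost her nothing. A woman seen only at six months would lose her measured weight if change were coded from baseline to 12 months and incomplete rows were deleted. The document states neither, so the number cannot be computed.

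**The case against.** The best defence is that bias needs the arm to affect the covariate, and nothing in the document shows that a weight programme alters marriage or employment. If it does not, the adjusted estimate is unchanged, as the first row of the table shows. These are also two items in a long list, and even the largest illustrated shift is under half a standard error. This stands as a limit on size and certainty. It does not justify the adjustment: the plan cannot know beforehand that the arm has no effect on these variables, and baseline values serve the purpose without the risk.

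Three stronger readings are tempting, and the document does not support them.
- **That lactation and smoking enter as follow-up values.** The Analysis plan gives no time point for either. Breastfeeding is recorded at every visit, so a baseline value exists, and Study aims lists breastfeeding status among baseline characteristics. Entrants must be non-smokers, but never and former smokers could still differ at entry. Only the silence on timing can be noted.
- **That the primary analysis becomes a completer analysis, losing up to 122 women (30% of 408).** That figure is the planned 12-month attrition, not a loss caused by covariates. No coding or deletion rule is stated, and the plan says that all measured weights are used.
- **That the effect is certainly biased, or biased towards zero.** Neither the presence nor the direction of bias follows from the text.

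**Conclusion.** Wrong as written. A model labelled intention-to-treat is committed to adjusting for at least one variable that the document itself collects after randomisation (employment change), and for a second whose wording implies it (marital-status change). This can bias the total effect in either direction if the arm affects these variables. The amount is unknown: between none and about 0.3 kg against the 2 kg target, wholly under the assumed parameters above. Loss of records is possible but depends on rules that the document does not state. The conclusion does not depend on the simulation, because the mismatch between the covariate and the estimand is enough to require the change.

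**What to change.** - Delete the change in marital status and the change in employment from the models for primary and secondary outcomes, including the logistic model for preconception weight that inherits the same predictors. Baseline marital status and employment may take their place.
- State once that every participant-level covariate in those models is a pre-randomisation value, naming lactation and smoking status explicitly. If baseline smoking status means never versus former, say so.
- Use follow-up changes in these variables only in the mediation or exploratory analyses that the Analysis plan already describes.

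The cost is a few words. The baseline values needed for lactation are already collected, and neither the sample size nor the stated power changes. Trial status describes recruitment as still open, so the change can be made before outcome data are analysed.

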### Randomization and masking

Randomization is computer-generated by the statistician. Specifically, randomization is conducted at the clinic level, stratified by county, and designed to ensure balance in treatment arms. Four clinics were crossed-over (in random order) in order to allow for estimation of some within-clinic effects. We decided to stratify randomization by county to control for any chance imbalance due to potentially unmeasured regional or administrative differences. We decided against further stratifying based on ethnicity and pre-pregnancy BMI due to the small likelihood of a chance imbalance, given the demographic similarity of the clinics, and limited evidence that these variables impact treatment response among postpartum (or other) women [83,84]. Within each randomized clinic, participants are sequentially selected until target sample sizes are met (please see Sample size calculation section**).**

Recruiters and assessors are blinded to the clinic randomization, and participants are not told their assigned treatment status until after enrollment. Several procedures are in place to ensure blinding among clinic recruiters, assessors, and potential enrollees. In brochures and the study consent form, the study is presented identically at both control and intervention clinics. There is a minimal amount of cross-over activity between clinics, but the study’s branded items are distributed at both intervention and control clinics as part of retention so that the study logo is a familiar sight. The recruiters and assessors have little to no contact with individuals aware of treatment assignment, including the WIC county chiefs and intervention research assistants.

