#### Sample size calculation

The targeted sample size (12 clinics; 34 participants per clinic; total N = 408) is projected to provide ≥80% power to detect a meaningful difference in weight change at 12 months as small as 2 kg between group means, when the standard deviation is 4.5 kg and the intraclass correlation (ICC) is 0.02, using a two-sided *t*-test with a significance level of 0.05, and accommodating anticipated rates of loss to follow-up (30% participant attrition at 12 months). Although we do not anticipate clinic attrition, 10 clinics (five in each condition) would provide 80% power to detect a difference in weight change as small as 2 kg. An ICC of 0.002 was estimated from results of our pilot demonstration trial and a WIC survey study [130], but we have conservatively used an ICC of 0.02 for sample size calculations [131]. For secondary aims, in our most conservative estimates [25], we would have greater than 80% power to detect both medium and large effects (Cohen’s d = 0.5 and 0.8, respectively) for any continuous or categorical outcome variable at the alpha = 0.05 level using a two-sided test of significance.

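### The primary model omits county, the randomisation stratum, yet commits five clinic-level covariates to 12 clinics; and the 10-clinic fallback has about 70% power, not 80%, on clinic-level degrees of freedom with the planned attrition

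*Protocol article*

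**What the plan says.** **Randomisation.** The Randomization and masking section allocates at clinic level: "We decided to stratify randomization by county". The stated reason is to guard against chance imbalance from unmeasured regional or administrative differences. There are three counties, with six, four and two clinics. Four clinics were also crossed over.

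**Model.** The Analysis plan says: "County is a stratification variable for randomization and is expected to be balanced across intervention and standard care groups by design". County does not appear in the list of model terms. The outcome is described as change from baseline in weight, but the treatment test is described as a group × time interaction in a repeated-measures mixed model with a random clinic effect. The participant-level covariates include lactation, age, education, socioeconomic status, and race and ethnicity. The plan then adds clinic-level terms, "including Latina proportion, lactation proportion, mean age, mean education, and mean SES".

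**Sample size.** The Sample size calculation section uses "12 clinics; 34 participants per clinic; total N = 408", targets a difference in "weight change at 12 months as small as 2 kg between group means", and applies "when the standard deviation is 4.5 kg and the intraclass correlation (ICC) is 0.02", with a two-sided *t*-test at 0.05 and 30% attrition. It claims at least 80% power. Clinic attrition is not expected, but the fallback statement is that "10 clinics (five in each condition) would provide 80% power" for the same 2 kg. The df of the *t*-test are not given, and the attrition is not repeated in the fallback sentence.

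**The concern.** Treatment is assigned to clinics, so in a parallel layout the comparison rests on 12 clinic-level observations with 10 df. Each term that varies only between clinics uses one of those df and, by chance correlation with treatment in so few clinics, inflates the variance of the treatment effect.

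The plan leaves out the one clinic-level factor that the design calls for. County was considered important enough to stratify on. Balance protects against bias, but it does not remove county-to-county variation from the error term. In its place the plan fits five factors that were not stratified on, and the sample size makes no allowance for them.

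Two things are at stake: the precision of the primary test under one of the two readings of the model, and whether the trial can lose two clinics without losing power, as the plan tells its readers.

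**Working it through.** **Inputs (Sample size calculation):** 6 clinics per arm (even split assumed), 34 women per clinic, 30% attrition, SD 4.5 kg, ICC 0.02, difference 2 kg, two-sided alpha 0.05. Sensitivity: "An ICC of 0.002 was estimated from results of our pilot demonstration trial".

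**Formulas.** Women analysed per clinic: m = 34 × 0.7 = 23.8. Design effect: DE = 1 + (m − 1) × ICC. SE = SD × √(2 × DE / (k × m)), with k clinics per arm. Power comes from the noncentral *t* with noncentrality 2/SE.

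**1. The plan's 12-clinic figure.** DE = 1 + 22.8 × 0.02 = 1.456. SE = 4.5 × √(2 × 1.456 / 142.8) = 0.643, noncentrality 3.11.
- Normal approximation: 87.5%
- *t* on participant-level df: 87.3%
- *t* on 10 clinic df: 80.1% (detectable difference 2.00 kg)

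The stated figure of at least 80% is met every way, with no slack on clinic df.

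**2. The 10-clinic fallback.** SE = 4.5 × √(2 × 1.456 / 119) = 0.704, noncentrality 2.84.
- Normal: 81.1%; *t* on participant-level df: 80.8%
- *t* on 8 clinic df: 70.2% (detectable difference 2.25 kg)
- *t* on 8 clinic df without attrition (m = 34, DE = 1.66, SE = 0.629): 79.5%
- *t* on 8 clinic df with attrition, ICC 0.002: 83.5%

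**3. Five clinic-level covariates, change score as dependent variable, group effect tested.** Clinic df: 10 − 5 = 5.
- Loss of df only (SE still 0.643): 70.3%; detectable difference 2.26 kg.
- With collinearity: for five random covariates on 12 clinics split 6 v 6, the expected variance inflation is (12 − 3)/(12 − 3 − 5) = 9/4 = 2.25, and simulation gives 2.26. Average power is 45% if the covariates explain nothing.
- If they explained all between-clinic variance, which is 0.02 × 23.8 / 1.456 = 33% of the clinic-mean variance, average power is about 59%.
- At ICC 0.002 (DE = 1.0456, SE = 0.545): 91.0% on 10 df, 83.2% on 5 df, about 57% on average with collinearity.
- Crediting the four crossed-over clinics (assumed: women split equally between arms, no clinic-by-period variance): SE falls to 0.596 and power without covariates is 85.5% on 10 df. The five terms raise the variance by about 39%, so SE = 0.596 × √1.39 = 0.703. Power is then about 63% on 5 df or 73% on 10 df. Within-clinic information raises the effective df, so the 5-df figure is on the low side.

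**4. The same covariates as main effects in a group × time model of weight.** Generalised least squares for 12 clinics × 34 women at 0, 6 and 12 months, with SD 4.5 and ICC 0.02 for change and the other variances assumed: the variance of the 12-month group × time effect is multiplied by 1.00, with complete data or with 30% dropout. It roughly doubles only if all five are also interacted with time, which the plan does not say.

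**5. County.** Three counties cost 2 df. The clinic counts of six, four and two allow an equal split within each county, so county would be orthogonal to treatment with no inflation. On 8 df at SE 0.643, power is 77.8% if county explains nothing. Fitting county on top of the five covariates would leave 3 df and 56.0%, so county should replace them rather than join them.

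**The case against.** The strongest objection is that the Analysis plan states a group × time test and mentions no covariate × time terms. On that reading the five clinic means shift a clinic's level at every visit and leave the treatment contrast untouched, as step 4 shows. This stands, and it makes the power loss conditional. It does not defend the terms: on this reading they do nothing for the contrast, and on the other reading, which follows the plan's own definition of the outcome, they harm it.

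A reader might infer that the 10-clinic 80% is an arithmetic error. The document does not support that. The usual large-sample design-effect calculation gives 81% for 10 clinics and 87.5% for 12, so a single method fits both statements. The df are not stated, and the fallback sentence does not repeat the attrition. The plan also does not expect to lose clinics, and calls its ICC of 0.02 conservative. What remains is that large-sample df are a poor approximation with ten clusters, and that the fallback follows directly from a calculation that includes attrition.

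A reader might also blame the omission of county for lost power. It is not the cause: fitting county costs about 2 points if it explains nothing, and the document reports no between-county variance. The omission is a mismatch between design and analysis.

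**Conclusion.** The point holds in three parts of different strength.

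- **County:** the stratification factor has no term in the primary model, and balance is not a substitute for one. This needs no assumptions.
- **Clinic-level covariates:** five terms on 12 clinics, duplicating participant-level adjustment, are not supported by the sample size. The cost depends on the reading. For a change score at ICC 0.02, power falls from 80% to 70% through df alone and to about 45% on average with chance collinearity in a parallel layout (about 57% at ICC 0.002), softened by the crossed-over clinics. For main effects in a group × time model, the cost is nil.
- **Fallback:** about 70% for 2 kg with 30% attrition, ICC 0.02 and 8 clinic df; 80% only for about 2.25 kg.

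The broader inference that the trial as designed does not deliver its stated power is not supported: 12 clinics without clinic-level covariates give 80.1% on 10 df.

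**What to change.** 1. Add county as a fixed effect in the primary model. Cost: 2 clinic-level df, taking power from 80% to 78% if county explains nothing.
2. Move the five clinic-level covariates to an exploratory or sensitivity model. The participant-level versions already cover the same constructs.
3. Test treatment with small-sample clinic-level df (Satterthwaite or Kenward-Roger).
4. Restate the fallback: 10 clinics give about 70% power for 2 kg, or 80% power for about 2.25 kg, at ICC 0.02 with 30% attrition. These figures are without county. With county fitted and explaining nothing, 6 df remain and power is about 66%, provided all three counties are still represented and balanced.

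All four are changes of wording. No extra clinics, women or data are needed; the only price beyond the county df is a less favourable fallback figure.

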### Eligibility criteria

Table 1 describes the eligibility and exclusion criteria for this trial. These criteria were selected to identify a representative postpartum population at greatest risk for weight gain and obesity-related co-morbidities. As indicated, women must be between six weeks and 12 months postpartum. Similar to other studies [24], we selected this period to strike a balance between allowing enough time for initial pregnancy-related weight loss to occur, while still intervening early enough to prevent long-term postpartum weight retention, which has been independently related to future weight gain and the development of obesity [15]. Women must be currently overweight or obese, with a body mass index (BMI) of 25 kg/m^2^or more or have a BMI between 22 and 24.9 and exceed pre-pregnancy weight by at least 4.5 kg (10 lb) [73]. On average, by six weeks postpartum, women retain 3 to 6.8 kg of the weight gained during pregnancy, with Hispanic populations falling into the higher end of this range [6,8]. A greater than 6.8 kg weight retention after six weeks postpartum would represent a significantly higher than average weight retention [6,8], increasing the risk of major weight gain later in life.

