**Table 1 Tab1:** **Inclusion and exclusion criteria for Fit Moms/**
***Mamás Activas***

**Inclusion criteria**	
	Between six weeks and 12 months postpartum
	BMI ≥25 kg/m^2^ or have a BMI between 22 and 24.9 25 kg/m^2^ and exceed pre-pregnancy weight by at least 4.5 kg (10 lb).
	18 to 40 years
	English- or Spanish-speaking
	Non-smoking
	Primiparous or multiparous
	Lactating or non-lactating
	Literacy ≥5^th^ grade level
	Cell phone

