#### Weight loss goals

Participants are given a scale and told to expect weight loss of 0.5 to 1 kg per week until reaching their weight loss goal. Women who are 10 pounds or more above their pre-pregnancy weight are encouraged to set an initial goal of getting back to their pre-pregnancy weight. Women who are within 10 pounds of their pre-pregnancy weight and overweight or obese are encouraged to set a 10% weight loss goal. Patients desiring to lose more weight are encouraged to do so, provided they maintain reasonable eating and activity patterns, and do not reduce below normal weight. Moderate weight loss does not appear to adversely affect lactation [23,74,75], but the study is monitoring such changes and tailoring goals accordingly.

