A secondary aim is to test the hypothesis that the intervention will result in a greater percentage of the women achieving their preconception weight or below at 12 months. For this analysis, a generalized linear mixed-model (binomial with a logit link) will be used for proportion at preconception weight or below at six and 12 months postpartum, including the same predictors described above. For secondary analyses comparing changes in behavioral and psychosocial variables, the effect of treatment at each time point will be investigated using the same basic linear mixed-effects model described above. In analyses of the possible differential effects of treatment on various subgroups of women, interactions between patient-level covariates (as in the main analyses) and group will be examined. A Bonferroni adjustment will be used to adjust for multiple comparisons. Also, generalized linear mixed-model analyses, as described above, will also be conducted to examine whether baseline variables moderate weight loss outcomes. Analyses of whether any effect of the intervention is mediated by differences in demographic, behavioral, and psychosocial factors will be conducted by first eliminating variables that have no impact on weight loss, then variables of interest will be entered into a final linear mixed-effects model, using both theoretical considerations to guide variable selection and the statistical strength of potential predictor variables [140].

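### The preconception-weight endpoint is timed from delivery although visits are timed from study entry; months since delivery is not a named covariate, and women already at that weight on entry can count as successes

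*Protocol article*

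**What the plan says.** On timing, the Analysis plan's secondary-aim paragraph specifies a binomial mixed model for the "proportion at preconception weight or below at six and 12 months postpartum". The sentence just before it gives the hypothesis at 12 months, and Study aims gives the outcome at six and 12 months; neither ties it to delivery. Study design and Outcome measures place assessments at baseline, six and 12 months.

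On entry, Table 1 admits women "Between six weeks and 12 months postpartum". Eligibility criteria explains the window as a balance between early intervention and "allowing enough time for initial pregnancy-related weight loss to occur".

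On covariates, the Analysis plan names participant-level items running from "lactation, age, age at menarche, education, income, smoking status, language, socioeconomic status" through race and ethnicity, height, pre-pregnancy BMI, parity, gestational gain, inter-pregnancy interval and baseline BMI to changes in marital status and employment. Time since delivery is not named. The preconception-weight model reuses the same predictors.

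On weight at entry, a BMI of 25 kg/m² or more is sufficient alone. Retention of at least 4.5 kg is required only for a BMI of 22 to 24.9. Weight loss goals plans for women close to their starting point: "Women who are within 10 pounds of their pre-pregnancy weight and overweight or obese are encouraged to set a 10% weight loss goal".

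**The concern.** A clock that starts at delivery and a clock that starts at enrolment differ by up to a year here. An analyst who follows the model sentence literally would look for weights that the schedule does not collect. One who follows Study aims would use the six- and 12-month visits. The endpoint should have one definition.

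The covariate list is detailed enough to include age at menarche, yet it leaves out the variable that the eligibility rationale itself links to weight loss after delivery. Two women with the same BMI and the same retained weight, one at six weeks and one at 11 months postpartum, may differ in the change to expect without treatment. If so, leaving timing out costs precision and leaves a chance imbalance between arms unadjusted, and only 12 clinics are randomised.

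The secondary hypothesis is about women achieving their preconception weight, but the modelled quantity is being at or below it. A woman already there at entry counts as a success if she is still there at follow-up. Such women make the observed difference less a measure of return to preconception weight.

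**Working it through.** **1. The plan's own power figure.** Inputs from Sample size calculation: 12 clinics of 34, difference 2 kg, SD 4.5 kg, ICC 0.02, two-sided alpha 0.05, 30% attrition.

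- Completers per clinic: 34 × 0.7 = 23.8.
- Design effect: 1 + (23.8 − 1) × 0.02 = 1.456.
- Effective women per arm: 6 × 23.8 / 1.456 = 98.1.
- Noncentrality: 2 / (4.5 × √(2/98.1)) = 3.11.
- Power: 80.1% with a t-test on 10 cluster degrees of freedom, 87.5% with the normal approximation.

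The stated 80% or more is reproduced.

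**2. Where the visits fall.** Entry is at 1.5 to 12 months postpartum. Visit time postpartum = entry time + 6 or + 12.

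| Entry (months postpartum) | Six-month visit | 12-month visit |
|---|---|---|
| 1.5 | 7.5 | 13.5 |
| 6 | 12 | 18 |
| 12 | 18 | 24 |

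The earliest follow-up weight is at 7.5 months, so none is taken at six months postpartum. A follow-up weight at 12 months postpartum needs entry at six months. A baseline weight coincides with six or 12 months postpartum for women who enter at those times, but it precedes treatment.

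**3. What the missing covariate could be worth.** The share R² of the variance in weight change explained by months since delivery is not in the document. Replacing the SD by 4.5 × √(1 − R²) in step 1, with 10 degrees of freedom:

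| Assumed R² | SD (kg) | Power |
|---|---|---|
| 0 | 4.50 | 80.1% |
| 0.05 | 4.39 | 82.0% |
| 0.10 | 4.27 | 84.0% |
| 0.15 | 4.15 | 86.0% |
| 0.20 | 4.02 | 87.9% |

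Chance imbalance, assuming uniform entry over 1.5 to 12 months: SD of timing = 10.5/√12 = 3.03 months. The SD of the between-arm difference is 3.03 × √(2 × DE/204), with DE = 1 + 33 × ICC. An assumed ICC of 0.02 (DE 1.66) gives 0.39 months; 0.10 (DE 4.30) gives 0.62 months. With an assumed natural change of 0.1 to 0.5 kg per month, a one-SD imbalance shifts the comparison by 0.1 × 0.39 = 0.04 kg to 0.5 × 0.62 = 0.31 kg, or about 2% to 16% of the 2 kg target. This treats all clinics as parallel. Four cross over, which should reduce the imbalance.

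**4. What women already at goal could do to the endpoint.** All inputs are assumptions: 20% at or below preconception weight at entry, 85% of them still there at follow-up in both arms, and success of 20% (standard) and 33% (intervention) among the rest.

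- Standard arm: 0.2 × 0.85 + 0.8 × 0.20 = 0.33.
- Intervention arm: 0.2 × 0.85 + 0.8 × 0.33 = 0.434.
- Difference: 10.4 points instead of 13.
- All women, 98.1 effective per arm: z = 0.104 / √((0.33 × 0.67 + 0.434 × 0.566)/98.1) = 1.51.
- Women above preconception weight only: 23.8 × 0.8 = 19.04 per clinic, design effect 1 + 18.04 × 0.02 = 1.361, effective n = 6 × 19.04/1.361 = 84.0 per arm, z = 0.13 / √((0.20 × 0.80 + 0.33 × 0.67)/84.0) = 1.93.

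These are crude proportions, not the adjusted model that the plan specifies.

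**The case against.** On timing, the intended meaning can be recovered from Study aims and from the preceding sentence of the Analysis plan, so a reader might call this a slip of one word. It is a little more than that, because the sentence that defines the modelled quantity is the one that is wrong. The opposite overstatement is also tempting: that the endpoint is unusable, or that no visit at all supplies a weight at 12 months postpartum. Neither is supported. The scheduled visits give a usable endpoint once the clock is corrected, and women who enter at six or 12 months postpartum do have a visit at 12 months postpartum.

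On the covariate, the list is introduced as inclusive and is meant to cover baseline differences and variables related to outcome, so months since delivery could be added within the text as it stands. Height, baseline BMI and pre-pregnancy BMI together already fix the weight retained at entry. Both points stand; what they leave out is timing. The eligibility rationale gives no month-by-month slope, so a steep decline at six weeks should not be read into it.

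On women already at goal, being at or below preconception weight is a valid status endpoint in all randomised women, and the model adjusts for baseline and pre-pregnancy BMI. A reader might infer that the restricted set ought to be the main analysis. The document does not support that: restriction gives up part of the randomised population, and the assumption of no treatment effect among women near goal sits badly with a programme that sets them a 10% loss goal.

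**Conclusion.** The timing point is a definite internal contradiction: the secondary endpoint as modelled cannot be computed for the cohort, and it conflicts with Study aims and the visit schedule. That conclusion needs only dates given in the document.

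Naming months since delivery is an improvement to the analysis rather than the correction of an error. The gain, from 80% power to about 82-88%, depends wholly on the assumed 5-20% of variance explained. A reader might infer that the primary comparison is biased without it. Under randomisation the issue is precision and chance imbalance, and the imbalance in the working is small beside 2 kg.

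Eligibility allows women to enter at or below preconception weight, but the document does not say how many will. The fall from 13 to about 10 points is an illustration only and justifies a supportive analysis, not a replacement. The primary outcome, the sample size and the stated power are unaffected.

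**What to change.** 1. In the secondary-aim paragraph of the Analysis plan, time the preconception-weight proportion at six and 12 months after baseline, in line with Study aims, Study design and Outcome measures.
2. Name months since delivery at baseline as a continuous covariate in the primary weight-change model and in the secondary models that reuse its predictors.
3. Keep all randomised women as the main preconception-weight analysis. Prespecify alongside it a supportive analysis of women above preconception weight at baseline, and report how many in each arm were already at or below it.

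The cost is a change of wording. Timing is known from eligibility screening, and current and pre-pregnancy weights are already collected. The supportive analysis uses fewer women and will be less precise to that extent.
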